### Aims

Specific aims are to achieve the Institute of Medicine (IOM) guidelines for postpartum weight loss and to improve maternal metabolic status by achieving and maintaining 1) postpartum weight reduction to prepregnancy weight if prepregnancy BMI was in the normal range, or to achieve a 5% reduction from prepregnancy weight if prepregnancy BMI was overweight/obese [27]; 2) at least 150 min per week of moderate intensity physical activity such as brisk walking, as recommended by ACOG for the postpartum period [28]; and 3) reduction in postpartum total energy intake via reduced consumption of popular energy-dense foods (e.g., fast food, high-fat snacks, fried foods and sugar-sweetened beverages), reduced portion size, appropriate modifications in ethnic recipes, and higher fruit and vegetable intake, as recommended by the ADA [29].

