### Outcome variables

Postpartum weight loss will be measured as the difference between weight at 6 or 12 months postpartum and weight at delivery, and will be calculated as absolute weight change according to prepregnancy BMI, percentage who retain a specific amount of weight over prepregnancy weight, or proportion whose BMI category changes from prepregnancy BMI category as have others (Table 1) [12-14].

**Table 1 T1:** Variables collected at assessment time points

	**Pregnancy**	**Postpartum**		
	**3rd trimester**	**6 wks**	**6 mos**	**12 mos**
**Aim #1: Postpartum weight loss**	X	X	X	X

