### Data analysis

Primary analyses will evaluate differences in the change from 6 weeks postpartum to 12 months postpartum between the groups (an intent to treat analysis) in postpartum weight loss (aim #1), biomarkers of insulin resistance (aim #2), and biomarkers of cardiovascular disease risk (aim #3). We will use mixed models with random subject effects, including a common mean at baseline for the treatment groups, a period effect, and an intervention by period interaction [60]. The mixed model analysis will enable inclusion of time varying covariates such as breastfeeding behaviors, depression, and sleep, which may vary between baseline and follow-up for individuals. Equivalence of treatment groups will be assessed by comparing distributions of the potential confounders across groups. In addition, we will investigate established risk factors for type 2 diabetes as potential confounders or effect modifiers. Important potential effect modifiers include prepregnancy BMI, and breastfeeding behaviors. Mixed model analyses will also be used to account for the repeated measures of exercise and diet and will be used to evaluate adoption and maintenance of behavior change (aim #4) in the Lifestyle Intervention group.

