### Power and sample size

The study is powered to detect mean differences in change in outcome variables from baseline in the Lifestyle Intervention as compared to the Health and Wellness (control) Intervention that are equivalent to 0.35 to 0.40 standard deviations, or a “small-medium” effect size [61], at 80% power at a 0.05 level of significance. A total of 256 women are required (128 participants per study arm). With an expected attrition rate of 15%, 300 eligible women will be recruited.

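### Weight and every listed biomarker are primary without ranking, the trial is sized for one test at 0.05, and the lead weight outcome is defined in two incompatible ways

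*Protocol article*

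**What the plan says.** All references are to the protocol article.

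- **Data analysis.** The primary, intent-to-treat analyses compare the arms on change from 6 weeks to 12 months postpartum "in postpartum weight loss (aim #1), biomarkers of insulin resistance (aim #2), and biomarkers of cardiovascular disease risk (aim #3"). No outcome is put ahead of another.
- **Table 1 (Outcome variables).** Aim 2 has 8 markers: glucose, insulin, HbA1c, adiponectin, leptin, TNF-α, HOMA and glucose AUC. Aim 3 has 9: total cholesterol, triglycerides, HDL, LDL, systolic and diastolic pressure, CRP, fetuin-A and albumin-to-creatinine ratio (ACR). ACR is marked in the third trimester only, although the text below the table counts it among the postpartum biomarkers.
- **Outcome variables.** Weight loss is the "difference between weight at 6 or 12 months postpartum and weight at delivery". It may be expressed as absolute change, or as "percentage who retain a specific amount of weight over prepregnancy weight, or proportion whose BMI category changes from prepregnancy BMI category". The amount retained is not given.
- **Aims.** The weight target is return to prepregnancy weight for women of normal prepregnancy BMI, "or to achieve a 5% reduction from prepregnancy weight if prepregnancy BMI was overweight/obese".
- **Power and sample size.** Differences in the outcome variables generally, "equivalent to 0.35 to 0.40 standard deviations", are to be detected "at 80% power at a 0.05 level of significance". "A total of 256 women are required (128 participants per study arm"), and "With an expected attrition rate of 15%, 300 eligible women will be recruited".

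**The concern.** A trial has one overall error rate for its primary claim. Here the primary claim is spread over weight and every listed biomarker without ranking, yet the only error rate stated is 0.05, and the sample size was derived as though there were one test. Read as written, a significant difference in any one marker is a primary result, and 0.05 is not the chance that the trial reports a false one.

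The natural lead outcome, weight, does not settle the matter because its definition is open. Two sections start the clock at different points (delivery against 6 weeks postpartum). One of them also leaves the visit and the scale to be chosen, and none of its scales measures the 5% reduction that the Aims set for overweight and obese women. A choice made after the data are seen would add to the error rate.

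**Working it through.** **1. Reproduce the plan's sample size.** Inputs from Power and sample size: effect 0.35 to 0.40 SD, 80% power, alpha 0.05, equal arms. Sidedness is not stated.

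n per arm = 2 × (z for alpha + z for power)² / d²

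- Two-sided, d = 0.35: 2 × (1.960 + 0.842)² / 0.1225 = 128.1, rounded up to 129, against 128 stated.
- Two-sided, d = 0.40: 99 per arm.
- One-sided: 101 and 78 per arm, which do not match.
- With 128 per arm, two-sided power is 80% at 0.35 SD and 89% at 0.40 SD.
- Attrition: 256 / 0.85 = 301.2, so 302, against 300 stated; conversely 300 × 0.85 = 255.

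The stated figures are therefore reproduced, within rounding, as one two-sided test at an unadjusted 0.05.

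**2. Count the primary outcomes.** Weight 1 + Aim 2 markers 8 + Aim 3 markers 9 = 18. As tabulated, ACR has no postpartum value and so no change from 6 weeks to 12 months, which leaves 17. Weight is counted once, because Data analysis fixes one contrast.

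**3. Chance of at least one false positive under no effect, each test two-sided at 0.05.** If independent, it is 1 − 0.95^m:

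- m = 17: 1 − 0.95^17 = 58.2%
- m = 18: 1 − 0.95^18 = 60.3%

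The outcomes will be correlated, but the document gives no correlations. The values below are assumptions. Test statistics were simulated as √ρ·G + √(1−ρ)·E, with G shared across outcomes and E separate for each, counting any absolute value above 1.96 (400,000 draws per cell).

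| Assumed pairwise correlation ρ | 17 outcomes | 18 outcomes |
|---|---|---|
| 0 (exact) | 58.2% | 60.3% |
| 0.3 | 49.3% | 50.9% |
| 0.5 | 38.6% | 39.8% |
| 0.7 | 27.1% | 27.7% |

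A block structure, with higher correlation within an aim than between aims, gives for 18 outcomes 54.7% (0.3 within, 0.1 between) and 46.6% (0.5 within, 0.2 between).

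**4. Could the stated size carry a full adjustment?** For scale only: Bonferroni over 18 tests uses 0.05 / 18 = 0.00278. That needs 240 per arm at 0.35 SD or 184 at 0.40 SD. With 128 per arm, power per test would be 42% to 58%. The sample size does not support 18 confirmatory tests.

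**5. Set the weight definitions side by side.**

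| | Outcome variables | Data analysis | Aims |
|---|---|---|---|
| Reference | delivery weight; prepregnancy for two of the scales | 6 weeks postpartum | prepregnancy weight |
| Visit | 6 or 12 months | 12 months | not tied to a visit |
| Scale | one of three alternatives | change in a mixed model | at prepregnancy weight, or 5% below it |

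Randomisation is at about 29 weeks' gestation, and the Introductory Phase, from then to delivery, already addresses gestational weight gain in the Lifestyle arm. Delivery weight and 6-week weight therefore both follow randomisation and may already differ by arm. Measuring change from either could remove part of the effect or distort it.

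**The case against.** The best defence is that this is a journal article. A multiplicity procedure, a testing order and exact endpoint derivations are commonly left to a full protocol or analysis plan, which is not shown. That stands as far as it goes: the absence of an adjustment is not the point here. The point is what the article does state, namely an unranked primary set, a sample size for one test, and two conflicting weight definitions. A later plan naming one primary outcome would depart from the Data analysis text, so the wording needs correction either way.

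Four stronger readings are tempting, and the document does not support them.

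- *Weight alone gives six primary tests (three scales at two visits).* Data analysis fixes a single contrast, and the scales are joined as alternatives. They are an open choice, not six co-primary tests.
- *A false-positive primary result is more likely than not.* That holds only under independence or weak correlation, up to about 0.3. HOMA sits beside glucose and insulin, total cholesterol beside its fractions, and systolic beside diastolic pressure, so independence is an upper end.
- *The Aim 1 goal would not be assessed at all.* With the retained amount set at zero, one of the listed scales would come close to the goal for women of normal BMI. Only the 5% reduction has no counterpart.
- *The plan declares success on any one significant outcome.* No such rule is stated. The error rates above describe what follows if each primary outcome is tested at 0.05 and read on its own.

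**Conclusion.** The point holds. Seventeen outcomes as tabulated (18 with postpartum ACR) are primary without ranking, while the sample size fits one two-sided test at 0.05. Tested each at that level under no effect, they give a 58% to 60% chance of at least one false-positive primary result if independent. For 18 tests the figures are about 40% and 28% at correlations of 0.5 and 0.7. That is roughly 5.5 to 12 times the nominal 5% (27.7 / 5 and 60.3 / 5). The correlations are assumptions, but the excess is large throughout this range.

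Separately, and without any assumption, Outcome variables and Data analysis disagree on the reference weight for the lead outcome. The former leaves visit and scale open, and none of its scales measures the 5% reduction in the Aims.

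**What to change.** - **One primary outcome.** Name continuous weight at 12 months postpartum.
- **One reference weight.** Reconcile Outcome variables with Data analysis. A weight from before randomisation (prepregnancy or enrolment) is preferable, for the reason in the working. If prepregnancy weight is chosen, state how it is obtained, since the article describes no measurement of it.
- **Power statement.** Say that the 0.05 level and the 80% power at 0.35 to 0.40 SD refer to this outcome. Check the SD of the chosen variable: the count of 128 per arm follows from the effect in SD units, but the difference in kilograms that it represents depends on that SD, so the stated power cannot simply be carried over.
- **Biomarkers and 6-month results.** Make them secondary. Either apply one multiplicity procedure, such as Holm, across Aims 2 and 3 together, or report them without confirmatory claims. Naming one lead marker per aim at 0.05 each would not be enough: for two independent tests the error is 1 − 0.95² = 9.75%. Gating the biomarkers on weight is optional.
- **Aim 1 goal.** Report attainment (prepregnancy weight, or 5% below it, according to prepregnancy BMI) as a supportive binary outcome in place of the list of alternatives.
- **ACR.** Reconcile Table 1 with the text on whether it is measured postpartum.

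The cost is wording in the protocol and analysis plan, plus the SD check. Weight keeps the full 0.05. The downside is that isolated biomarker results can no longer be presented as primary findings.

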### Lifestyle intervention

The Lifestyle Intervention is an evidence-based approach utilizing culturally and linguistically modified, motivationally targeted, individually-tailored intervention materials developed in our prior randomised controlled trials among Hispanics [32-39]. The intervention draws from Social Cognitive Theory [40] and the Transtheoretical Model [41] and takes into account findings by our research group on the specific social, cultural, economic, and environmental resources as well as challenges faced by women of Hispanic backgrounds [25,42,43].

The Introductory Phase (~29 weeks gestation - delivery) (Figure 1) will start with a face-to-face session. The goal of this phase is to optimize gestational weight gain for the remaining pregnancy period and move women over the continuum of pre-contemplation to contemplation and preparation for the postpartum Active Intervention Phase. Motivational interviewing principles will be used to identify and strengthen women’s motivations for change. Specifically, the session will target knowledge and attitudes regarding gestational weight gain, postpartum weight loss, and type 2 diabetes prevention. Gestational weight gain guidelines will be reviewed and participants will be provided with a digital scale.

The session will additionally include administration of diet and physical activity questionnaires that facilitate tailoring the intervention. The Diet Tailoring Questionnaire is a two-part survey consisting of a checklist of high-calorie and lower-calorie foods and beverages commonly consumed by the target population. Respondents are asked to indicate the frequency that they consume the various foods and rate their confidence (self-efficacy) in their ability to decrease high calorie and increase low calorie food consumption. The Exercise Tailoring Questionnaire consists of 3 measures: Stages of Change for Physical Activity [44], Processes of Change for Physical Activity [45], and Self-Efficacy for Physical Activity [44].

This session will be followed by a third trimester booster telephone counseling session which will review progress toward gestational weight gain management and reinforce preparation for postpartum weight loss. Print-based intervention materials, in Spanish or English depending upon participant preference and written at a 6th grade reading level, will be mailed.

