### Covariates

Clinical characteristics of the current pregnancy and medical history will be abstracted from the pregnancy medical record (Table 1). Weight is measured prospectively at each prenatal visit and postpartum weight will be measured during assessment visits by trained study staff to the nearest 0.1 kg on accurately calibrated standard clinical scales using a standardized protocol. Gestational age will be based upon the best clinical estimate as recorded in the medical record. Adherence with gestational weight gain guidelines will be calculated by comparing the observed weight gain with the 2009 IOM Guidelines [27]. We will also collect gestational age at the time of GDM screen; degree of abnormality on glucose tolerance testing during pregnancy; treatment for glucose abnormality during pregnancy (e.g., diet, oral hypoglycemic agents and/or insulin); pregnancy complications; and birth outcomes.

Sociodemographic factors will be collected via self-report at enrollment. Acculturation will be assessed via the Psychological Acculturation Scale [55], language preference, and generation in the U.S. Smoking will also be assessed via the biomarker cotinine. Postpartum factors will be collected via self-report at each postpartum assessment and will include: The Pittsburgh Sleep Quality Index (PSQI) [56], the Edinburgh Postpartum Depression Scale [57,58], and the Infant Feeding Questionnaire [59].

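### The primary intent-to-treat model is left open to adjustment for breastfeeding, depression and sleep, all measured only after randomisation

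*Protocol article*

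**What the plan says.** The Data analysis section sets the primary comparison as the between-arm difference in change from 6 weeks to 12 months postpartum, labelled intent to treat, for aims 1 to 3. The model terms it fixes are random subject effects, a common baseline mean, a period effect and an intervention-by-period interaction. The next sentence gives an advantage of this model: it "will enable inclusion of time varying covariates such as breastfeeding behaviors, depression, and sleep". The same paragraph adds two further statements: "Equivalence of treatment groups will be assessed by comparing distributions of the potential confounders across groups", and "Important potential effect modifiers include prepregnancy BMI, and breastfeeding behaviors".

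Under Randomisation, allocation takes place at about 29 weeks of gestation. Table 1 marks the postpartum factors (sleep, depression, breastfeeding) at 6 weeks, 6 months and 12 months, with no mark in the third-trimester column. The Covariates section likewise has them self-reported at the postpartum assessments.

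Gestational weight gain is listed among the covariates in Table 1, and the Covariates section says "Adherence with gestational weight gain guidelines will be calculated by comparing the observed weight gain with the 2009 IOM Guidelines". The Lifestyle intervention section makes it a target of the Introductory Phase: "The goal of this phase is to optimize gestational weight gain for the remaining pregnancy period".

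**The concern.** A covariate recorded after allocation can itself be a result of allocation. Adjusting for it then changes what the treatment coefficient means, in two ways. If the intervention moves the covariate and the covariate moves the outcome, adjustment removes that part of the effect (mediation). If the covariate and the outcome share an unmeasured cause, conditioning on the covariate links allocation to that cause (a collider path), and randomisation no longer protects the comparison.

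Both routes are plausible here. The booster calls deal with caregiving load, social support and partner negotiation, which bear on mood and sleep. Activity and weight loss may do so as well. Breastfeeding is tied to the dietary part of the intervention, because the calorie goal in the Curriculum section depends on it for some women.

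Using breastfeeding as an effect modifier has a related weakness. Women who breastfeed in one arm and women who breastfeed in the other are groups formed after allocation, so comparing them is not a randomised comparison.

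At stake is whether the headline estimates for aims 1 to 3 are the total intent-to-treat effects that the section promises.

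**Working it through.** **1. Timing.** Randomisation: about 29 weeks. Intervention start: the same time, with the Introductory Phase running to delivery. First record of breastfeeding, depression and sleep: 6 weeks postpartum. As described, none of the three has a pre-randomisation value, so any adjustment for them uses values taken under the intervention.

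**2. The plan's own figure.** Inputs from Power and sample size: "equivalent to 0.35 to 0.40 standard deviations", "at 80% power at a 0.05 level of significance", and "A total of 256 women are required (128 participants per study arm"). Two-sided testing is assumed, since the article does not say.

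- n per arm at 0.35 SD = 2 × (1.960 + 0.842)² / 0.35² = 128.1, rounded up to 129 (stated: 128).
- Standard error of the standardised difference with 128 per arm = √(2/128) = 0.125. Power = Φ(0.35/0.125 − 1.96) = Φ(0.84) = 80.0%.
- Recruitment: 256 / 0.85 = 301.2, so 302 (stated: 300).

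The design figures are reproduced to within rounding. At the lower end of the effect range there is no spare power.

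**3. Illustration: part of the effect runs through the covariates.** The documents give no mediated share, so 0% to 50% is assumed. Remaining effect = total × (1 − share). Power = Φ(remaining/0.125 − 1.96), with the residual variance held constant.

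| Assumed share | Left of 0.35 SD | Power | Left of 0.40 SD | Power |
|---|---|---|---|---|
| 0% | 0.350 | 80% | 0.40 | 89% |
| 10% | 0.315 | 71% | 0.36 | 82% |
| 20% | 0.280 | 61% | 0.32 | 73% |
| 30% | 0.245 | 50% | 0.28 | 61% |
| 50% | 0.175 | 29% | 0.20 | 36% |

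**4. Illustration: mediation and a shared cause together.** This is a linear model at one time point, simpler than the trial's mixed model. Let A be arm, U an unmeasured cause, and M the covariate:

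- M = a·A + g·U + noise, with variance 1 within arm
- Y = (0.35 − a·b)·A + b·M + g·U + noise

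The total effect is 0.35 by construction. The coefficient of A after adjusting for M is 0.35 − a·b − a·g². Simulation with 200,000 subjects per setting agrees:

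| a | b | g | Unadjusted | Adjusted | Formula |
|---|---|---|---|---|---|
| 0 | 0.3 | 0.5 | 0.348 | 0.345 | 0.35 |
| 0.2 | 0.3 | 0 | 0.347 | 0.288 | 0.29 |
| 0.4 | 0.3 | 0 | 0.350 | 0.230 | 0.23 |
| 0.2 | 0 | 0.5 | 0.347 | 0.298 | 0.30 |
| 0.4 | 0 | 0.5 | 0.350 | 0.252 | 0.25 |
| 0.2 | 0.3 | 0.5 | 0.349 | 0.243 | 0.24 |
| 0.4 | 0.3 | 0.5 | 0.346 | 0.126 | 0.13 |

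The unadjusted estimate stays near 0.35 throughout. With a = 0 adjustment does no harm. The rows all move downward because every non-zero coefficient was set positive. If U raised M but lowered Y, the last term would be + a·g², so the direction is not fixed either.

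**The case against.** The strongest reply is that the article has not chosen to adjust. The terms it fixes contain no covariate, the sentence on time-varying covariates describes what the method allows, and the comparison is labelled intent to treat. The exact covariate list is the kind of detail that a journal article leaves to the full protocol or SAP. This stands in part: it rules out saying that the primary model will adjust. It does not remove the point, because the article goes beyond silence. It names three specific post-randomisation variables within the primary-analysis paragraph, offers their inclusion as a benefit, and does not confine them to secondary work.

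Three stronger readings are tempting and are not supported.

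- A reader might infer that gestational weight gain is a primary-model term. The Data analysis section never names it. It could enter only through the general wording on confounders, and part of the gain precedes randomisation.
- A reader might infer that covariates will be picked according to observed imbalance, so that the p-value loses its meaning. The text says only that distributions will be compared and risk factors investigated. It does not say that imbalance decides what enters the model.
- A reader might take the power losses above as a forecast. The shares are assumed, and the calculation ignores any gain in precision from prognostic covariates. The stated intervention targets are weight, activity and diet, not sleep, mood or breastfeeding. Contact is also scheduled alike in both arms, so a shift would have to come from content.

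Effect modification by breastfeeding is likewise only a potential analysis, not the primary estimate.

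**Conclusion.** The point holds as an opening left in the primary analysis, not as an error already committed. The plan permits adjustment of the primary intent-to-treat model for breastfeeding, depression and sleep, and proposes breastfeeding as an effect modifier, although all three arise after randomisation. If they are included, the estimate is the total randomised effect only on the assumption that the intervention leaves them unchanged. Otherwise, mediation or collider bias may follow.

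The documents do not allow its size or sign to be worked out. The figures above show only that moderate assumed paths would matter in a trial with about 80% power at 0.35 SD, and that there is no such bias when the intervention does not affect the covariates. The statement that the primary estimate will be biased goes further than the text.

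**What to change.** State that the primary model for aims 1 to 3 contains the common baseline mean, period and intervention-by-period terms, plus only prespecified pre-randomisation covariates: the OGTT randomisation stratum and, if wanted, prepregnancy BMI. Add that no covariate enters because of an observed difference between arms. The enrolment value of the outcome should not be added as a further covariate by default, since the common baseline mean may already carry it.

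Move any model with breastfeeding, depression or sleep to analyses labelled exploratory or mediation. Do the same for gestational weight gain, if it is used at all, because the Introductory Phase targets it. Limit effect-modifier analyses presented as randomised comparisons to pre-randomisation variables such as prepregnancy BMI and OGTT stratum.

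The cost is wording only. Data collection and sample size do not change. What is given up is any precision that the postpartum covariates would have brought to the primary model.

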**Aim #4: Behavioral outcomes**				
Physical activity (actigraph, PPAQ)	X	X	X	X
Dietary intake (24-hr recalls)	X	X	X	X

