### Behavioral outcomes

Women will be provided with the ActiGraph GT3X-plus activity monitor to be worn on the wrist for 7-days at each of the assessment time periods (enrollment, 6-weeks, 6-months, and 12-months postpartum). Previous studies have reported reasonable validity under laboratory conditions among pregnant women [50], as well as under free-living conditions [51-53]. In addition, at each assessment time period, trained bilingual personnel blinded to the assigned intervention arm will conduct three unannounced 24-hr dietary recalls over a two-week period and administer the Pregnancy Physical Activity Questionnaire (PPAQ) [54]. The PPAQ is a semi-quantitative questionnaire which evaluates participation in household/caregiving, occupational, sports/exercise, and transportation activities.

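### The only analysis stated for aim #4 (physical activity and diet) follows the Lifestyle arm over time; no between-arm contrast is stated, although the behavioural measurements are not restricted by arm.

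*Protocol article*

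**What the plan says.** In the Data analysis section, the between-arm commitment reads "Primary analyses will evaluate differences in the change from 6 weeks postpartum to 12 months postpartum between the groups (an intent to treat analysis"). The outcomes then listed are postpartum weight loss (aim #1), biomarkers of insulin resistance (aim #2) "and biomarkers of cardiovascular disease risk (aim #3"). Aim #4 is not in the list. The model is a mixed model with random subject effects, a baseline mean shared by the two arms, a period effect and an intervention-by-period interaction.

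Aim #4 comes at the end of the section, in one sentence with two parts. The first part is "Mixed model analyses will also be used to account for the repeated measures of exercise and diet" and names no arm. The second says that the models "will be used to evaluate adoption and maintenance of behavior change (aim #4) in the Lifestyle Intervention group".

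Table 1 has a block headed "Aim #4: Behavioral outcomes", which contains "Physical activity (actigraph, PPAQ") and dietary intake by 24-hour recall, marked at the third trimester, 6 weeks, 6 months and 12 months. Under Behavioral outcomes, "trained bilingual personnel blinded to the assigned intervention arm will conduct three unannounced 24-hr dietary recalls over a two-week period" at each assessment and also administer the activity questionnaire. No restriction by arm is given.

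**The concern.** Measurement runs from late pregnancy to a year after delivery. Over that time activity and intake may change for reasons unrelated to the intervention: recovery from delivery, feeding, sleep and repeated measurement. The Data analysis section itself names breastfeeding, depression and sleep as factors that may vary between baseline and follow-up. Within one arm, the period effect contains all of this together with any effect of the intervention. Randomisation and a control arm free of diet and exercise content are there to separate the two.

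The error can run either way. If activity rises equally in both arms, the Lifestyle trajectory alone looks like adoption. If activity is flat in the Lifestyle arm and falls in the control arm, the Lifestyle trajectory alone hides a benefit. An analysis plan that carried the aim #4 sentence forward literally would leave a numbered aim without a randomised comparison.

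**Working it through.** **1. What is stated, aim by aim (Data analysis and Table 1)**

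| Aim | Outcomes | Comparison stated |
|---|---|---|
| #1 | Weight loss | Between arms, intent to treat |
| #2 | Insulin-resistance biomarkers | Between arms, intent to treat |
| #3 | Cardiovascular biomarkers | Between arms, intent to treat |
| #4 | Physical activity, diet | Adoption and maintenance in the Lifestyle arm |

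**2. Is a comparator available?** Blinding assessors to arm serves a purpose only if both arms are assessed. The Health & Wellness section describes a control arm with mailings and calls on the same schedule, on topics other than exercise and diet. The comparator that aim #4 needs is therefore already in the design.

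**3. The plan's own sample size (Power and sample size)**

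Inputs: a between-arm difference in change of 0.35 to 0.40 SD, 80% power and a 0.05 level. Two-sided testing is assumed because sidedness is not stated.

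- n per arm = 2 × (1.960 + 0.842)² / 0.35² = 128.1, rounded up to 129, or 258 in total. The plan says 128 per arm, 256 in total.
- 256 / 0.85 = 301.2, rounded up to 302. The plan says 300, and 300 × 0.85 = 255.

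The stated figures reproduce to within rounding, so no number in the plan is wrong here.

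**4. Power of a between-arm contrast for aim #4 with the planned women**

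Power = Φ(d × √(128/2) − 1.960) = Φ(8d − 1.960):

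- d = 0.35: Φ(0.840) = 80.0%
- d = 0.40: Φ(1.240) = 89.3%

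**5. Illustration of the within-arm test**

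Assumptions, not figures from the document: both arms shift by the same s (in SDs of the change score), the intervention has no effect, and 128 women are analysed in the Lifestyle arm.

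P(significant) = Φ(s√128 − 1.960) + Φ(−s√128 − 1.960), with √128 = 11.314.

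| Shared shift s | s√128 | Within-arm test significant | Between-arm test significant |
|---|---|---|---|
| 0 | 0 | 5% | 5% |
| 0.1 | 1.131 | 20% | 5% |
| 0.2 | 2.263 | 62% | 5% |
| 0.3 | 3.394 | 92% | 5% |

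The between-arm column stays at 5% because the expected difference is s − s = 0.

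**The case against.** The strongest reply is that the text does not say the control arm will be left out. The first part of the aim #4 sentence names no arm, and its wording ties back to a model with an intervention-by-period term. The power section speaks of differences between arms in outcome variables generally, and Table 1 lists behaviour among the outcomes. A reader might infer that the plan rules out any between-arm analysis of behaviour. That goes too far: a Lifestyle-only analysis is the natural reading of the sentence, not an explicit exclusion. What remains is that no between-arm contrast for aim #4 is stated anywhere, while a single-arm one is.

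A second reply is that adoption and maintenance among treated women is a fair descriptive question, in line with the Active and Maintenance Phases. This stands. The document also does not say that a within-arm change will be reported as an intervention effect. The percentages above are errors only if the change is attributed to the intervention; as a test of change over time, the within-arm test does its job.

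Third, the size rests on assumed shifts, because the document gives no figure for ordinary postpartum change in activity or diet. That also stands.

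Finally, a reader might infer that the trial could then not show that behaviour change explains a weight effect. The document does not support this. It promises no mediation analysis, behavioural measurement is not limited to one arm, and a between-arm test of behaviour would not by itself establish mediation.

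**Conclusion.** The point holds as a gap in the stated analysis of a non-primary aim. Followed as written, aim #4 is an uncontrolled before-after analysis that cannot separate an intervention effect from ordinary postpartum change. This rests on two readings: that the arm named in the sentence is the analysis population, and that both arms are measured, which follows from the blinding and the absence of any restriction by arm. The rise from 5% to about 20%, 62% or 92% is an illustration under assumed shared shifts of 0.1 to 0.3 SD, not an estimate for this trial. The comparisons for aims #1 to #3 and the sample size are unaffected.

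**What to change.** Make three changes to the Data analysis text:

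- State for aim #4 a between-arm intervention-by-period contrast in all randomised women, using the mixed model already specified for aims #1 to #3, with its common baseline mean.
- Name the reference time. The primary analyses use change from 6 weeks postpartum, whereas the power section refers to change from baseline. Randomisation takes place at about 29 weeks of gestation, after the baseline assessment, so the enrolment measurement is the only one taken before it. It is therefore the only one at which randomisation justifies a common mean. If 6 weeks is kept as the reference for aim #4, the text should say so and acknowledge that the Introductory Phase has already been delivered by then.
- Label the within-Lifestyle analysis of adoption and maintenance descriptive.

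The cost is two or three sentences. No added women, visits or measurements are needed, and the planned 128 per arm already give 80% to 89% power at 0.35 to 0.40 SD. The change should be made before the data are analysed by arm.
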